**Comparison unit**

Wards allocated to the control arm (passive control group) will continue with their usual care, and staff will not receive additional education offered by the trial team. There are no restrictions on how nursing staff work in these wards, although participation in corresponding projects is not supported. Any workshop seminars, local meetings, outreach visits or structured monitoring or support will not be organised in the comparison wards. As in the intervention hospital organisations, any analysis of the current treatment problems or possible quality gaps to be shared with the staff members will not be collected or shared by interviews or observations. Any information packages aiming to support their positive treatment culture will not be shared with the staff members working in these hospital organisations. The trial team will contact the control wards only to collect baseline data of the wards and the outcome data. After the 18 months intervention and follow-up period, comparison wards will be given a possibility to participate in workshops and seminar related to the intervention.

**Measures****Background information**

Patients: The demographic information of the patients (age, gender, marital status, educational level, housing, employment status, number of psychiatric hospital treatment periods, the time of first contact with psychiatric services) will be collected as part of a patient follow-up survey.

## SUPPLEMENT 1

Demographics of unit of randomisation: The following information about the units will be described: a number of hospital beds, a number of patients, bed/patient ratio, a number of treatment periods, an average length of stay, gender ratio, patient average age, three most common diagnose (ICD-10) [76], and a number of staff/professional group. In addition, a short description of the ward type and treatment methods will be asked.

### Primary outcome

#### *Organisational outcomes*

The primary outcome of the study is the incidence of seclusion room use by patients in each unit. This will be assessed based on local (and national, if possible) health registers (Finnish Mental Health Act 1116/1990, [70]). The outcome will be measured at three time points: baseline (in 2015) based on local register (at the end of 2016), year 2016 (at the beginning of 2017), and year 2017 (at the beginning of year 2018). Information collected from each organisation is comparable across hospital organisations. The national register holder, Care Register for Health Care [71] gives instructions on how the information regarding treatment notifications shall be collected, recorded and sent annually to the National Institute of Health and Welfare. To ensure that the information about incidence of seclusions can be obtained in full detail, data will be collected either manually based on nurses' notes and/or medical registers at the local organisations.

### Secondary outcomes

#### *Organisational outcomes*

Other types of coercive measures: incidence of other types of coercive measures used on patients (limb restraint, forced injection, physical restraint) according to the Finnish Mental Health Act (1116/1990, [70]) (yes/no), including the frequency and/or length (in minutes, if possible) of these measures. The outcome will be measured at three time points: baseline based on local register from year 2015 (at the end of 2016), year 2016 (at the beginning of 2017), and year 2017 (at the beginning of year 2018). Information to be collected in each organisation will be comparable based on the instructions of data recording by the National Institute of Health and Welfare. The data will be collected either manually based on nurses' notes and/or medical registers at the local organisations.

Service use (collected from local and/or national registers): type of admission, length of stay (days), death [yes]. The data will be collected either manually based on nurses' notes and/or medical registers at the local organisations. Information to be collected in each organisation is comparable based on the instructions of data recording by the National Institute of Health and Welfare [71]. The outcome will be measured at three time points: baseline based on local register from year 2015 (at the end of 2016), year 2016 (at the beginning of 2017), and year 2017 (at the beginning of year 2018).

#### *Staff outcomes*

Team climate among nursing teams (Team Climate Inventory, TCI, 38 items [77, 78]) will be surveyed at baseline and 18-20 months after beginning of the intervention. The inventory consists of four subscales; participative safety, support for innovation, vision and task orientation. Items in subscales of participative safety and support for innovation are measured with 5-point Likert-type scale, while subscales of vision and task orientation are measured with 7-point Likert-type scale. Higher scores indicate better team climate [78]. In the Finnish population, subscales of the inventory have demonstrated high internal consistency (Participative safety  $\alpha = 0.88$ ; Support for innovation  $\alpha = 0.87$ ; Vision  $\alpha = 0.95$ , Task orientation  $\alpha = 0.91$  [79]) and moderate correlations ( $r = 0.36-0.48$ ) with other methods assessing team innovativeness [80].

Turnover will be measured at baseline (based on local register data from 2015), year 2016 (at the beginning of 2017), and year 2017 (at the beginning of year 2018).

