### **Data analysis**

#### *Statistical analysis*

The Data Management Committee including a statistician outside of the research team will verify the statistical analysis and the Quality Assurance Process.

The baseline characteristics of the units, and respondents (patients, staff members) will be summarised using descriptive analysis (mean [standard deviation], median [interquartile ranges] or proportions) and compared between each intervention group, respectively.

The analysis will be carried out on an intent-to-treat (ITT) basis. Assumptions of normality of the residuals will be investigated. For the primary outcome, incidence of coercion methods used at the baseline (year 2015), year 2016 (at the beginning of 2017), and year 2017 (at the beginning of year 2018) will be calculated. Possible differences in patient characteristics between the intervention and the control group at baseline will be tested by Chi-Square or t-tests based on type of variables. This analysis will help to decide whether baseline characteristics of patients should be adjusted for in the model for the primary outcome comparison after intervention. The hierarchical (participant nested within ward) Poisson model will be used to estimate and test the relative risk of being coerced in the intervention and the control group, which takes into account the length of staying of patient's in hospitals. With the same principle, for secondary outcomes, a hierarchical linear model will be used for normally distributed variables such as patient satisfaction and team climate, a hierarchical logistic model for dichotomous outcomes such as any admission or any adverse event, and the Poisson model for hospitalisation stay lengths or time spent in a seclusion room. A sensitivity analysis will be conducted by comparing the primary data at the follow-up and the fidelity information [47]. If poor fidelity was found for the primary data, we may consider evaluating change rate of coercive methods use between the two groups using all three measures over time by applying repeatedly measured models with random effects of hospital clusters. The results from the secondary analyses will be treated as exploratory. Estimates and confidence intervals will be reported only. The CONSORT guidelines for randomised trials [95] will be followed throughout our data analysis and the reporting of our study results. This study protocol follows the recommendations of the SPIRIT Statement [96].

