### Declarations

#### *Ethics approval and consent to participate*

The preparation phase of the trial (focus group interviews with staff members, and patients and relatives in associations) has been approved by the Ethics Committee of the University of Turku (33/2015). The proposal related to national register data has been assessed by the Ethics Committee of the University of Turku (code 41/2015). The trial has been approved by the Ethics Committee of the Hospital District of Southwest Finland (ETMK:9/1801/2016) and permissions to conduct the pilot study and realise the study in psychiatric hospitals have been granted by the study organisations in 2016. The study has been registered with ClinicalTrials.gov (NCT02724748 [99]).

Interviews with staff members, patient groups and relatives will be done on a voluntary basis and written informed consent will be obtained. The unit staff/research team members will approach patients and their relatives to explain the purpose of the study and its arrangements both directly and in written format. Patients and their relatives will be given the opportunity to ask questions about the study. Those assessed as lacking the capacity to give informed consent, and those who decline to participate, will not be interviewed. Staff and patient surveys are voluntary and will not include names, social security numbers, or any other identifiable information.

Participants will be informed that they have the possibility to withdraw their consent, and they will be made aware that data collected before withdrawal may be used for research purposes. Participants will also be informed that refusal or withdrawal from the study will not affect their position as staff members, health care clients or have effect on their relative's care.

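### Team climate is surveyed before and after the intervention, but the stated model gives the baseline wave no role, so the comparison reads as post-intervention only

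*Protocol*

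**What the plan says.** Protocol, Staff outcomes: the Team Climate Inventory has four subscales, two with 5-point and two with 7-point items, and "will be surveyed at baseline and 18-20 months after beginning of the intervention". The model is in Statistical analysis: "a hierarchical linear model will be used for normally distributed variables such as patient satisfaction and team climate". Under Patient outcomes, patient satisfaction is first measured 9 months after the intervention starts, so it has no baseline.

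Statistical analysis says four things that bear on baseline data:

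- Description: "The baseline characteristics of the units, and respondents (patients, staff members) will be summarised using descriptive analysis", with a comparison between arms.
- Adjustment: patient characteristics are tested between arms at baseline, and "This analysis will help to decide whether baseline characteristics of patients should be adjusted for in the model for the primary outcome comparison after intervention".
- Carry-over: the secondary models are introduced by "With the same principle, for secondary outcomes".
- Repeated measures: if fidelity is poor, the team may consider "evaluating change rate of coercive methods use between the two groups using all three measures over time".

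None of these makes the baseline team climate score a term in a model.

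Under Recruitment and randomisation, the hospital organisation is the randomised unit, stratified by bed count and size of the nursing staff. Study status reports 15 hospitals with 28 wards.

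**The concern.** One clause specifies the model for two outcomes, one with a baseline wave and one without, and does not say how that wave is used. The adjustment rule covers patient characteristics, which cannot stand in for a score rated by staff. The repeated-measures model is conditional and covers coercive methods only. The natural reading is therefore a comparison of the arms at 18-20 months.

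Supporting team climate is part of the study aim and of the intervention's name. Few hospitals are randomised and team climate is not a stratification factor, so the arms may well differ before the education begins. A follow-up comparison leaves that difference in the estimate to the extent that climate persists. The baseline survey that could remove part of it is already planned.

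**Working it through.** **1. The plan's own figure.** The protocol states no power or precision for team climate. Its only power figure concerns the primary outcome, and it reproduces. The design effect is 1 + (265 − 1) × 0.005 = 2.32. The effective number per arm is 7 × 265 / 2.32 = 799.6. The standard error is √[(0.11 × 0.89 + 0.07 × 0.93) / 799.6] = 0.0143. Power is Φ(0.04 / 0.0143 − 1.96) = 80%. It has no bearing on team climate.

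**2. Inputs.** From the protocol: 15 hospitals, with the hospital as the randomised unit. Assumed: a 7 v 8 split, because the hospital split by arm is not given; and a correlation *r* between a hospital's baseline and follow-up means, shown as a range because the protocol gives no SD, intracluster correlation or correlation over time for this inventory. Stratification is ignored.

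**3. Chance baseline difference.** In units of the SD between hospitals, its standard deviation is √(1/7 + 1/8) = 0.52. Under normality, the difference exceeds 0.5 with probability 2[1 − Φ(0.5/0.52)] = 0.33, and exceeds 1 with probability 0.05.

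**4. Effect of adjusting.** In a hospital-level analysis, baseline adjustment multiplies the variance by (1 − r²), costs one degree of freedom, and carries an expected penalty of 1 + 1/(n − 4) for imbalance in the covariate. With n = 15:

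width factor = (t on 12 df / t on 13 df) × √[(1 − r²)(1 + 1/11)] = (2.179 / 2.160) × 1.044 × √(1 − r²) = 1.053 × √(1 − r²)

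Without adjustment, a baseline difference *d* moves the follow-up estimate by r × d (equal SDs at the two waves). The last column takes d = 0.52.

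| r | √(1 − r²) | Interval width factor | Carry-over, r × 0.52 |
|---|---|---|---|
| 0 | 1.000 | 1.05 | 0 |
| 0.3 | 0.954 | 1.00 | 0.16 |
| 0.5 | 0.866 | 0.91 | 0.26 |
| 0.7 | 0.714 | 0.75 | 0.36 |
| 0.8 | 0.600 | 0.63 | 0.41 |

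Break-even is where 1 − r² = 1/1.053² = 0.90, so r is about 0.31.

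**5. On the scale of individual scores.** If the hospital-level intracluster correlation were 0.05 to 0.20 (assumed), one between-hospital SD would be √0.05 = 0.22 to √0.20 = 0.45 individual SDs. The 0.52 then equals 0.12 to 0.23 individual SDs. Of that, 0.06 to 0.12 reaches the estimate at r = 0.5, and 0.09 to 0.19 at r = 0.8.

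**6. Sensitivity to the unit.** Study status says that wards were randomised, 13 v 15. Treating wards as independent units, the SD in step 3 becomes √(1/13 + 1/15) = 0.38. The width factors are 1.02, 0.98, 0.89 and 0.61 at r = 0, 0.3, 0.5 and 0.8. The pattern is the same.

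**The case against.** The strongest reply is that this is silence and not error. The protocol names a class of model, and such a model can hold a baseline covariate or both waves. Covariates of a secondary model are often left to the analysis plan, which is not at hand, and the phrase "With the same principle, for secondary outcomes" leaves some room for adjustment. This stands in part: nothing excludes a baseline term. But the section does fix rules for the use of baseline data, and none reaches team climate.

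Three stronger readings are tempting, and the documents do not support them.

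- **Anonymity makes the baseline unusable.** A reader might infer this from "Staff and patient surveys are voluntary and will not include names, social security numbers, or any other identifiable information". It rules out pairing one person's two answers on the plan as described. It does not rule out ward or hospital means, which need no personal identifier.
- **The baseline wave is wasted.** The protocol gives the baseline characteristics of staff respondents a descriptive role and a comparison between arms, and it does not bar further use.
- **A follow-up-only comparison is biased.** Under randomisation it is unbiased on average, and a properly clustered interval already allows for chance differences between hospitals. The loss is precision, together with distortion of the particular estimate obtained.

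The stakes are also limited: "The results from the secondary analyses will be treated as exploratory", and team climate is listed beside staff turnover without ranking. Exploratory status lowers the importance but does not remove the point, because estimates and intervals are what will be reported.

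**Conclusion.** The point holds as a minor one. The protocol collects a baseline team climate score and, read as written, does not use it in the treatment comparison. With 7 v 8 hospitals, the chance baseline difference has an SD of about 0.52 between-hospital SDs.

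The benefit of adjustment depends on the assumed correlation of hospital means over time. The interval is about 5% wider at r = 0, unchanged at about 0.3, 9% narrower at 0.5 and 37% narrower at 0.8. The method is better only if climate is moderately stable within hospitals over 18-20 months, which is plausible but is not documented in the protocol. The figures also rest on the assumed split and on a hospital-level simplification.

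**What to change.** Add one sentence to Statistical analysis. For each Team Climate Inventory subscale, the 18-20 month model includes the ward (or hospital) baseline mean of that subscale as a covariate, with hospital, as the randomised unit, and ward as random effects.

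The alternative is one mixed model for both waves with an arm-by-time term and the same random effects. Two details then matter. The arms should share a common baseline mean; otherwise the model compares changes, whose hospital-level variance factor is 2(1 − r), for example 2 × 0.7 = 1.4 at r = 0.3, which is worse than follow-up alone. A cluster-by-time effect is also needed, so that the correlation over time is estimated and not set to one.

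Choose between the two before follow-up data are seen.

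The cost is one covariate and about one degree of freedom, with a slightly wider interval if the correlation proves low. No new measurement and no linkage of individuals is needed. The forms must carry a ward code; the protocol does not say whether they do, so confirm it.

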#### *Patient outcomes*

The functional capacity of patients (Global Assessment Scale, GAS [81]), rated by staff members at the time of the discharge process, will be assessed. The value of the measure can vary between 0 and 100. Higher scores indicate better functional capacity of patients [81]. The scale has demonstrated high inter-rater reliability ( $r = 0.72$ ) and significant correlation ( $r = -0.64$ ) with other scales used to assess the symptom complexity of patients [82]. The measuring of this outcome will begin 9 months after beginning of the intervention (at the beginning of 2017).

## SUPPLEMENT 1

Patient treatment satisfaction (Client Satisfaction Questionnaire, CSQ-8, 8 items [83]) will be assessed with a structured paper survey for every patient at the time of their discharge process. Patients respond to the questions using a 4-point Likert scale. Responses are scored from 1 to 4, and thus the possible total scores range from 8 to 32. Higher scores indicate greater satisfaction with treatment [83]. The survey has demonstrated a high level of internal consistency (Cronbachs'  $\alpha$  0.92) and significant correlation ( $r = 0.67$ ) to other methods used to measure treatment satisfaction [84]. The measuring of this outcome will begin 9 months after beginning of the intervention (at the beginning of 2017).

Quality of Life (Quality of Life Enjoyment and Satisfaction Questionnaire-Short Form, Q-LES-Q-SF, 16 items [85]) will be assessed with a structured paper survey for every patient at the time of their discharge process. Each of the 16 items is rated on a 5-point scale that indicates the degree of enjoyment or satisfaction experienced during the past week. Higher scores on indicate greater contentment or satisfaction [85]. In the Finnish psychiatric patient population, this instrument has demonstrated high internal consistency (Cronbachs'  $\alpha = 0.89$ ) and moderate correlation with other methods used to assess quality of life ( $r = 0.445$ ) [86]. The measuring of this outcome will begin 9 months after beginning of the intervention (at the beginning of 2017).

### **Feasibility of the intervention**

Feasibility of the intervention will be analysed from organisation, staff members, and patients' point of views. Acceptability (willingness of patients to participate, satisfaction with the intervention, willingness to continue the intervention), implementation (degree of execution), integration (drop out), and practicality (easy to use, yes/no) [87], in daily practice will be assessed at the end of the study.

### **Fidelity and quality components of the intervention**

The fidelity of the intervention and staff adherence to the intervention will be supported and assessed (Table 2). Each item completed achieves a score of 0-1.00, giving a total percentage of 0%-100%. Lastly, the final seminar will be organised by the team in conjunction with the intervention units.

*Table 2 about here*

The strengths, weaknesses, opportunities, and threats related to the new practices will also be discussed and categorised based on a SWOT analysis. Possible barriers and facilitating factors for change in each unit will be identified during workshops and outreach visits. Further, to gain a deeper understanding of staff members' willingness to engage themselves in the new approach in practice, interviews will be conducted at the last phase of the study for staff members, patients and relatives. Their perceptions of human treatment environment with the following topics will also be assessed: a) Uniqueness of the individual; b) Real choices; c) Attitudes and rights; d) Dignity and respect; e) Partnership and communication; and f) Evaluating recovery-oriented mental health practice [73]. Convenience sample method will be used to recruit participants into the interviews ( $N = 50\%$  staff members and patients from a unit and  $25\%$  patients' relatives will be interviewed [73]). In addition, their opinions about the possible changes at the units will be discussed.

### **Data management**

All original paper and electronic data will be managed and held in accordance with the University of Turku and the national standards of the Finnish Personal Data Act (523/1999, [88]), partner organisations' special requirements, and the health care organisations' policies and national acts. The Council for International Organizations of Medical Sciences (CIOMS [89]) and the Declaration of Helsinki [90] will be followed, to ensure confidentiality of data. The material for the study will be mainly obtained from local registers, case notes and national health registers, and through patient and staff surveys. Data will be in paper and electronic format and saved electronically for statistical analysis. The qualitative data will be digitally recorded and transcribed to be analysed in written format. Members of the DMC are representatives from the ethical board, mental health associations, hospitals and hospital districts, national health and welfare institute, and statistics. Their role is to support, advice and evaluate the trial as well as intervention and outcomes. They also provide guidance related to financing, modifications, timing, risk management and quality assurance. The DMC have meetings twice a year.

### **Power and sample size**

We have systematically searched for, but found no directly relevant past work [31, 91]. We assume that if the data will be obtained from local hospital registers by sampling 7 clusters (hospitals) with 265 subjects each in intervention group and 7 clusters with 265 subjects each in control group, we will have 80% power to detect a difference between the

## SUPPLEMENT 1

group proportions of -0.0400. The control group proportion is 0.1100. The intervention group proportion is assumed to be 0.1100 under the null hypothesis and 0.0700 under the alternative hypothesis. The test statistic used is the two-sided Z test (unpooled) with an overall significance level at 0.05. We may assume based on the hospital registers that sample size for the total population admitted in the study wards in one year will be 3710. However, if we consider a loss of 20% patients in the local care registers, [92] the total number of patients on the randomised wards should be about 4454 patients. (PASS 11 software [93]). Further, if we assume 50% response rate for patient survey [94] out of possible 3710 participants, we will assume that we will obtain 928 filled questionnaires during 6 month survey data collection period. The sample size calculation was adjusted for intra-cluster correlation at 0.005.

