### Study status

To date, we have recruited 15 hospitals, in which a total of 28 psychiatric wards are willing to participate. Wards were randomised in May 2016 (13 intervention wards, 15 in comparison wards).

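### The stated 80% power rests on a normal reference with 14 equal hospitals; with hospital-based degrees of freedom it is 73% as planned and about 70–76% for the 15 recruited, before allowing for unequal sizes

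*Protocol*

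**What the plan says.** The Protocol, section Power and sample size, assumes "7 clusters (hospitals) with 265 subjects each in intervention group" and "7 clusters with 265 subjects each in control group". It states that "we will have 80% power to detect a difference between the" two "group proportions of -0.0400". The reference rate is fixed: "The control group proportion is 0.1100", against 0.07 under the alternative. The test is specified as follows: "The test statistic used is the two-sided Z test (unpooled) with an overall significance level at 0.05". On clustering it says: "The sample size calculation was adjusted for intra-cluster correlation at 0.005".

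The same section gives 3,710 as the expected one-year total and 4,454 as the number needed to cover a 20% loss in the registers. It gives no source for the ICC, no range around it, and no allowance for hospitals of different size. It does say that a systematic search found nothing directly relevant.

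The section on recruitment and randomisation makes the hospital organisation the unit of randomisation, stratified by beds and nursing staff. The section Study status reports: "To date, we have recruited 15 hospitals, in which a total of 28 psychiatric wards are willing to participate".

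**The concern.** When whole hospitals are randomised, treatment varies only between hospitals. The error of the comparison is then estimated from 14 or 15 hospital-level units, not from thousands of patients. A design effect corrects the size of the standard error, but not the uncertainty in estimating it from so few units. That second correction comes from a t reference with degrees of freedom equal to the number of hospitals minus two, and the power section does not make it.

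Two further inputs point the same way. Every hospital is taken to have exactly 265 patients, although 28 wards cannot divide equally among 15 hospitals and randomisation was stratified by size. The ICC of 0.005 also has no stated basis, although with 265 patients per hospital it largely determines the answer.

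At stake is how the result will be read. A null finding would be presented as coming from a trial with 80% power when the design has less, and possibly much less.

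**Working it through.** **Inputs from the protocol:** 7 + 7 hospitals, m = 265, rates 0.11 and 0.07, ICC 0.005, two-sided 0.05, 15 hospitals recruited, 3,710 and 4,454 patients, 20% loss. **Assumed:** the 7/8 split of the 15 hospitals, the coefficients of variation (CV) of hospital size, and the alternative ICC values. The protocol gives none of these.

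**1. Reproducing the stated figure.**
- Design effect = 1 + (265 − 1) × 0.005 = 2.32.
- Effective n per arm = 7 × 265 / 2.32 = 1,855 / 2.32 = 799.6.
- SE = √[(0.11 × 0.89 + 0.07 × 0.93) / 799.6] = √[(0.0979 + 0.0651) / 799.6] = 0.01428.
- Noncentrality = 0.04 / 0.01428 = 2.80.
- Power with critical value 1.96 = Φ(2.80 − 1.96) = 80.0%.

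The protocol's figure is therefore correct for the test it names.

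**2. Same inputs, hospital-based df.** With 14 − 2 = 12 df the critical value is 2.179. The noncentral t with noncentrality 2.80 gives power of **73.0%**.

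**3. Fifteen hospitals, 13 df (critical value 2.160), equal sizes, ICC 0.005.** The range in each row reflects which arm holds the eighth hospital: the lower figure applies if it is the intervention arm, the higher if it is control.

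| Patients analysed | Per hospital | Power, t(13) |
|---|---|---|
| 3,710 | 247.3 | 74.5–75.6% |
| 4,454 × 0.8 = 3,563 | 237.5 | 73.7–74.8% |
| 3,710 × 0.8 = 2,968 | 197.9 | 70.0–71.1% |

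**4. Unequal hospitals.** Design effect = 1 + [(1 + CV²) × m − 1] × ICC. With 7 + 7 hospitals, mean size 265, ICC 0.005 and t(12):

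| CV (assumed) | Design effect | Power |
|---|---|---|
| 0.3 | 2.44 | 71% |
| 0.4 | 2.53 | 69% |
| 0.5 | 2.65 | 67% |
| 0.6 | 2.80 | 65% |

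**5. Sensitivity to the ICC**, 7 + 7 hospitals of 265:

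| ICC | Design effect | Power, Z | Power, t(12) |
|---|---|---|---|
| 0.005 (protocol) | 2.32 | 80.0% | 73.0% |
| 0.01 (assumed) | 3.64 | 61% | 54% |
| 0.02 (assumed) | 6.28 | 40% | 35% |

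For scale, an ICC of 0.005 corresponds to a between-hospital SD of √(0.005 × 0.11 × 0.89) = 0.022, or 2.2 percentage points around 11%.

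**6. Conditional type I error.** If a hospital-level statistic on 12 or 13 df were compared with 1.96, its two-sided error would be 2 × P(t > 1.96) = 7.4% or 7.2%.

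**The case against.** Several counter-arguments have force.

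**The Z test is not the planned analysis.** It appears only in the sample-size statement. The Statistical analysis section plans a hierarchical Poisson model that accounts for length of stay, and it states no df method. A reader might infer that the trial will be tested at an error rate of about 7%. The protocol does not support that: the figure holds only if a normal reference is used at hospital level, and the df method may be set in an analysis plan that is not shown. The objection does not rescue the 80%, which the protocol itself ties to a Z test.

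**The wards might be the clusters.** Study status speaks of wards being randomised, 13 against 15. With 28 wards as independent clusters, 26 df and the same ICC, the same method gives about 88–89%. But the sections on setting, randomisation and sample size all name the hospital as the cluster, and the power calculation is built on it.

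**The 20% loss is already addressed.** The 4,454 figure is an allowance for it, so taking the loss off 3,710 is only one reading. Because 3,710 is also described as the expected one-year total, it is unclear whether 4,454 can be reached. Both readings are shown above.

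**The large drops are hypothetical.** The CVs and higher ICCs are assumed. A reader might infer that 0.005 is too low or that true power is near 35–54%. Nothing in the protocol shows that. What stands is that so influential a value has no stated basis or sensitivity range.

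**The two-proportion basis is a simplification.** Stratification or baseline adjustment could move power either way. The recalculation deliberately stays on the protocol's own basis.

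**Conclusion.** The point holds. The 80% is right for a normal reference with 14 hospitals of exactly 265 patients, but that reference does not fit a comparison on 12 or 13 df. On the protocol's own inputs power is 73.0%, a shortfall of 7 points. The 73% belongs to 12 df only. For the hospitals actually recruited it is about 70–76%, so the shortfall is roughly 4 to 10 points, depending on the number analysed and on the assumed 7/8 split.

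The direction of the effect of unequal sizes is certain, because ward counts cannot be equal, but its size depends on a CV that the protocol does not give. The dependence on the ICC is steep, and the protocol neither sources 0.005 nor shows what happens if it is wrong. All of this rests on the hospital being the unit of randomisation. This is a misstatement of power that should be corrected. It does not show that the primary test will be invalid.

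**What to change.** - Replace the 80% with power for the hospitals as recruited: the actual hospital split, t with hospital-based df, and the observed variation in hospital size. At ICC 0.005 and before allowing for unequal sizes, expect about 70–76%. State which number of patients analysed the figure assumes.
- Show power at ICC 0.01 and 0.02 beside 0.005, and check 0.005 against the hospital-level seclusion rates in the 2015 baseline register data.
- If the primary test would otherwise use a normal reference at hospital level, give it the same hospital-based df. This item is conditional, because the protocol does not state the df method. If the analysis plan already sets one, a cross-reference is enough.

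The cost is a recalculation and some rewording. No extra hospitals or patients are needed. The only downside is a less favourable stated power.

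### The allowance for a 20% register loss multiplies by about 1.2 instead of dividing by 0.8, and the plan does not say whether 3,710 is counted before or after that loss

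*Protocol*

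**What the plan says.** All of this is in the protocol, section *Power and sample size*.

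- The design is obtained "by sampling 7 clusters (hospitals) with 265 subjects each in intervention group and 7 clusters with 265 subjects each in control group", which is 14 × 265 = 3,710 patients, for 80% power.
- "The control group proportion is 0.1100", against 0.07 in the intervention arm if the alternative is true.
- "The test statistic used is the two-sided Z test (unpooled) with an overall significance level at 0.05". The intra-cluster correlation (ICC) is 0.005.
- From the hospital registers, the "sample size for the total population admitted in the study wards in one year will be 3710".
- With 20% of patients lost in the local care registers, "the total number of patients on the randomised wards should be about 4454 patients".

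The section names no additional wards, hospitals or time from which patients beyond 3,710 would come. *Study status* reports 15 recruited hospitals with 28 wards. It gives the split of wards by arm but not the split of hospitals.

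**The concern.** Two things do not fit together.

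First, an allowance for loss should return the required number once the loss is taken off. Taking 20% off 4,454 does not give back 3,710.

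Second, 3,710 plays two roles: the number needed with data for 80% power, and the number expected to be admitted in a year. If the admitted number is counted before register loss, the allowance asks for more patients than the plan expects to have, and the power after loss is not stated anywhere.

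What is at stake is how the result is read. If the primary comparison shows no difference, readers will judge it against 80% power. They should know whether that power holds under the loss the plan itself allows for.

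**Working it through.** **Inputs** (all from *Power and sample size*): K = 7 hospitals per arm, m = 265 patients per hospital, p1 = 0.11, p2 = 0.07, ICC = 0.005, two-sided α = 0.05, unpooled Z test, loss 20%, one-year intake 3,710.

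**Formulas**

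- Design effect: DE = 1 + (m − 1) × ICC
- Effective number per arm: n = K × m / DE
- Standard error: SE = √{[p1(1 − p1) + p2(1 − p2)] / n} = √{(0.0979 + 0.0651) / n} = √(0.163 / n)
- Power = Φ(0.04 / SE − 1.96)

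**Step 1. Reproduce the plan's power.** DE = 1 + 264 × 0.005 = 2.32. n = 1,855 / 2.32 = 799.6. SE = 0.01428 and 0.04 / SE = 2.802. Power = Φ(0.842) = 0.800. The plan's figure is reproduced. With 264 per hospital power is 0.799, so 265 has no slack and 3,710 is the number needed with data.

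**Step 2. Check the allowance for loss.**

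- Stated: 4,454. Compare 3,710 × 1.2 = 4,452, which is within 2 patients.
- Needed: 3,710 / 0.8 = 4,637.5, so 4,638. The stated figure is 184 too low.
- Check: 4,454 × 0.8 = 3,563, and 3,710 − 3,563 = 147 short.

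**Step 3. Power under each count**, with 14 hospitals of equal size:

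| Starting number | After 20% loss | Per hospital | DE | Effective n per arm | Power |
|---|---|---|---|---|---|
| 4,638 | 3,710 | 265 | 2.32 | 799.6 | 80.0% |
| 4,454 | 3,563 | 254.5 | 2.268 | 785.7 | 79.3% |
| 3,710 | 2,968 | 212 | 2.055 | 722.1 | 75.9% |

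The fall is modest because patients within a hospital are correlated: at a design effect above 2, losing a fifth of the patients costs about a tenth of the effective sample (722.1 / 799.6 = 0.90).

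**Step 4. Use the recruited number of hospitals.** Assume the 15 hospitals split 7 and 8 and that 2,968 patients are spread evenly, 197.9 per hospital. DE = 1.984, and the effective numbers are 698.0 (7 hospitals) and 797.7 (8 hospitals). Power is 76.6% if the intervention arm has 8 hospitals and 77.7% if the control arm has 8.

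**The case against.** The strongest reply concerns the second part. The 3,710 is described as based on hospital registers, and the loss is a loss in registers. If records missing from the register are already absent from the 3,710, taking off another 20% counts the loss twice, and the 76% does not apply. The text does not rule this out. The survey estimate in the same section uses 3,710 as a yearly count (3,710 × 50% response × half a year = 927.5, stated as 928), but that does not settle whether the count is before or after loss. This objection stands, so the shortfall is conditional. It does not rescue 4,454, which fails its own check under either reading.

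It can also be said that patients are not enrolled to a target: primary-outcome data come from registers for the study wards, so correcting the figure changes nothing in conduct. *Primary outcome* further plans collection from nurses' notes and/or medical registers so that seclusions are captured in full, and the 20% is worded as a contingency. Both points are fair and limit the weight of the finding.

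Three stronger readings are tempting and are not supported:

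- *That the stated 80% power is wrong.* It is right for its stated condition, 265 patients with data in each of 14 hospitals. The section does not claim 80% at 3,710 admitted with 20% lost.
- *That the patients required cannot exist.* This would follow only if 3,710 were known to be before loss.
- *That power is far lower still once a t reference with 12 degrees of freedom is used.* That is a separate question about the test. It gives 73.0% before any loss, and the loss takes off about 4 points under either test.

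**Conclusion.** The error in the allowance is certain: 4,454 should be 4,638. Its effect is small, 80.0% to 79.3%.

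The larger matter is conditional. If 3,710 is the intake before register loss, about 2,968 patients are analysable and power is about 76% with the planned 14 hospitals, or about 77% to 78% with the 15 recruited, given the assumed 7/8 split and even spread. If 3,710 is already net of loss, that shortfall disappears and only the wrong total remains.

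The figures keep the plan's proportions, ICC and Z test. They also assume that loss is random and equal across hospitals and arms. Severity is minor to moderate.

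**What to change.** In *Power and sample size*:

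1. Replace 4,454 with 4,638.
2. State whether 3,710 is counted before or after register loss.
3. If before, add that about 2,968 patients are expected to be analysable at 20% loss, with power of about 76%, beside the 80% that applies with no loss. If the hospital split by arm is available, the figure can be given for the 15 recruited hospitals instead.

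The cost is a few figures and one or two sentences in one section. Design, enrolment and analysis are unchanged. If 3,710 is before loss, the stated power becomes slightly less favourable.
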